### Population

Inclusion criteria are adult patients (≥18 years old) with a radiological diagnosis of IPMN and/or documented treatment with GLP-1 RAs, availability of medical records including laboratory results and imaging studies and signed informed consent permitting the use of anonymized clinical data for research. Eligible individuals will then be classified into one of four groups:

Patients with GLP-1 RA exposure and IPMNPatients with GLP-1 RA exposure without IPMNPatients without GLP-1 RA exposure with IPMNPatients without GLP-1 RA exposure and without IPMN = general population

Exclusion criteria is refusal of consent for research participation.

### Data collection

Data will be extracted from electronic medical records and include demographic information (age, sex, BMI), clinical and family history, comorbidities (e.g., diabetes, dyslipidemia, hypertension), laboratory values (HbA1c, fasting glucose, lipase, amylase, CA19−9, CEA), and imaging findings. Study data will be collected and managed using REDCap electronic data capture tools hosted at University of Fribourg [20,21]. REDCap database is available as S2 File. Data collection will start on September 2025 and is expected to be completed by March 2026. Results are expected to be published by November 2026. S3 File illustrates a detailed schedule for enrolment, data collection and assessment.

### Outcomes

#### Primary outcome.

Changes in IPMN radiological characteristics based on criteria from the Kyoto 2023 Consensus [1].

#### Secondary outcomes.

Changes in serum tumor markers (CA19-9, CEA) over timeIncidence of AP

### Hypotesis

Our Hypothesis are illustrated in Fig 1.

### Radiological evaluation

MRI is the preferred imaging modality; CT scans will be included if MRI is unavailable. Two senior radiologists at HFR will independently and blinded to prior findings assess imaging studies with the internationally recognized semiological criteria for assessing cystic pancreatic lesions on cross-sectional imaging: high-risk stigmata and worrisome features (cyst diameter, enhancing mural nodules, thickened or enhancing cyst walls, main pancreatic duct diameter, change in calibre, lymphadenopathy, cystic growth). In addition, morphological and signal analysis criteria of the pancreatic gland will be analysed (glandular volume, T1 and T2 weighted signal, diffusion restriction). Furthermore, radiological assessments will be used to monitor for any signs of pancreatitis, such as pancreatic inflammation or fluid collections, that may be associated with GLP-1 RA therapy.

### Sample size and statistical analysis

#### Sampling plan.

The sample size is expected to be between 10 and 20 patients for the condition with GLP-1 RAs and IPMN, due to the rare nature of the patient population with both IPMN and GLP-1 RA use. The other conditions (GLP-1 RA & no-IPMN, no GLP-1 RA & IPMN) will match in sample size the above-mentioned condition as it is the most stringent. This design ensures to isolate the interaction effect of GLP-1 RA and IPMN while ensuring proper statistical power. Indeed, a-priori power analysis computed with G*Power [22] shows that for our smallest estimation of effect size (i.e., 10–30 patients per condition, 30–60 in total), a 2x2 ANOVA detects a significant medium effect size with a power if 80% and an alpha of 0.05.

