**Discussion:**

This study aims to explore potential associations between GLP-1 RA use and changes in IPMN characteristics, tumour markers, and disease progression. Given the retrospective design and expected small sample size (estimated at 30–60 patients in total), the study may not be powered to establish definitive correlations. Nonetheless, it will generate preliminary data to help inform hypotheses and guide future research. Any observed trends could provide valuable insights into the safety of GLP-1 RAs in patients with IPMNs and contribute to more informed clinical decision-making regarding the use of these agents in a population at risk for pancreatic disease progression.

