#### Analysis plan.

H1) We expect significantly more occurrences of change in at least one of the criteria from the Kyoto 2023 Consensus (see Outcomes section) [1] from patients with GLP-1 RA & IPMN than patients with no GLP-1 RA & IPMN, as assessed by a one-sided test of two proportions. H2) We expect significantly greater changes in the CEA (H2a) and CA19−9 (H2b) serum tumor markers over time induced by GLP-1 RA, as assessed by the interaction term of the within-factor Time and the between-factor Group (GLP-1 RA & IPMN vs. no GLP-1 RA & IPMN). H3) We expect significantly different incidence of AP driven by GLP-1 RA and IPMN, as assessed by a Chi-square test across all conditions (GLP-1 RA & IPMN, no GLP-1 RA & IPMN, GLP-1 RA & no IPMN).

Timing of progression: T0 will be defined as the first available follow-up examination for patients with IPMN who were not treated with GLP-1 RAs, and as the first available follow-up examination after initiation of GLP-1 RA therapy for patients with IPMN who received GLP-1 RAs.

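### The claimed 80% power for a medium effect does not follow: the named 2x2 ANOVA has about 26–48% at 30–60 patients and is not the primary test

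*Protocol article*

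**What the plan says.** The Sampling plan (under Sample size and statistical analysis) starts from the scarcest group: "The sample size is expected to be between 10 and 20 patients for the condition with GLP-1 RAs and IPMN". The other two sampled groups "will match in sample size the above-mentioned condition". It says the design isolates the GLP-1 RA by IPMN interaction with adequate power. In support it cites a G*Power calculation for "10–30 patients per condition, 30–60 in total", concluding that "a 2x2 ANOVA detects a significant medium effect size with a power if 80% and an alpha of 0.05".

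The Analysis plan contains no GLP-1 RA by IPMN ANOVA:

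- H1, on the primary outcome, compares the two IPMN groups, "as assessed by a one-sided test of two proportions".
- H2 (tumour markers) is a Time by Group interaction in the same two groups.
- H3 (acute pancreatitis) is a chi-square test across three groups.

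Under Study design (text following the Fig 1 legend), the fourth cell of the 2x2 has no sampled patients; a general-population incidence of acute pancreatitis stands in for it. The Discussion part of the abstract says "the study may not be powered to establish definitive correlations".

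**The concern.** Thirty to sixty patients is far below what a medium effect in a between-patient 2x2 ANOVA usually needs, so the 80% looked doubtful. It is also attached to an analysis that the plan does not contain and that three sampled cells cannot support, so the primary test has no power statement of its own.

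The section is not consistent internally either. It gives 10–20 and then 10–30 patients per condition, and it calls a patient count an effect size.

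The question is one of drug safety, and the Fig 1 legend hypothesises no increase in progression. If H1 is not significant and the reader believes the study had 80% power for a medium effect, the result will be taken as evidence against harm. At the true power, such a result would be common even if a medium effect existed.

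**Working it through.** **Inputs from the protocol.** Alpha 0.05; power 80%; effect described only as medium; 30–60 patients in total; 10–20 in each of three sampled groups; the 2x2 is GLP-1 RA (yes/no) by IPMN (yes/no), both between patients; H1 is one-sided on two groups.

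**Assumptions.** Medium is f = 0.25 for ANOVA and h = 0.5 for two proportions. The control risk for H1 is not given; 20% is used, with 10–30% as the range. One-sided alpha for H1 is taken as 0.05.

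**1. The plan's own figure.** For a fixed-effects ANOVA with one numerator degree of freedom, power = P(F′ > F-critical), where F′ is noncentral F with λ = f²N and df = (1, N − 4).

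| N | λ = 0.0625 × N | Power |
|---|---|---|
| 30 | 1.875 | 26.1% |
| 40 | 2.5 | 33.7% |
| 60 | 3.75 | 47.7% |
| 90 | 5.625 | 65.0% |
| 128 | 8.0 | 80.1% |

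The stated 80% is not reproduced. It needs 128 patients, 32 per cell. At 80% power the smallest detectable f is 0.53 with 30 patients and 0.37 with 60.

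**2. Other between-patient readings.**

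- Three cells instead of four (df2 = N − 3): 26.2% at N = 30 and 47.8% at N = 60.
- Three-group one-way ANOVA (df1 = 2): 19.5% and 37.4%; 80% needs 158 patients.
- Alpha 0.10: 37.9% and 60.6%.
- A large effect, f = 0.40: 56.0% and 86.1%, reaching 80% at 52 patients. That is not the effect claimed.

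**3. The primary test, H1.** With h = 0.5, power = Φ(h√(n/2) − 1.645):

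- n = 10 per group: Φ(1.118 − 1.645) = 29.9%.
- n = 20 per group: Φ(1.581 − 1.645) = 47.5%.
- n for 80%: 2 × ((1.645 + 0.842)/0.5)² ≈ 49.5, so about 50 per group.

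On the risk scale, exact binomial enumeration of the pooled one-sided z-test gives 25% power (n = 10) and 41% (n = 20) for 20% versus 40%. The exposed risk needed for 80% power is:

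| Assumed control risk | n = 10 per group | n = 20 per group |
|---|---|---|
| 10% | 59% | 43% |
| 20% | 71% | 58% |
| 30% | 81% | 69% |

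Precision is correspondingly poor. For 20% versus 40%, the Wald 95% half-width is 1.96 × √((0.2×0.8 + 0.4×0.6)/n), which is ±39 percentage points at n = 10 and ±28 at n = 20.

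**4. Group sizes.** Three groups of 10–20 give 30–60, which matches the stated total. Three groups of 10–30 give 30–90, which does not.

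**The case against.** The strongest counter-argument is that the figure may come from a different 2x2. H2 is a Group by Time analysis; with two groups and two time points it too is a 2x2 ANOVA. At f = 0.25 with an assumed correlation of 0.5 between repeated measures, it reaches 80% at 34 patients, inside the stated range. This may be how the number arose, but it does not rescue the statement:

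- The Sampling plan names the GLP-1 RA by IPMN interaction and gives neither a correlation nor a number of measurements.
- H2 uses only the two IPMN groups, 20–40 patients, so power at that correlation runs from 56% to 87%. At correlation 0 it is 32–59%, at 0.3 it is 43–74%, and at 0.7 it is 78–98%.
- H2 is a secondary outcome.

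Second, f = 0.25 is a convention the protocol does not state. That is true, and the 26–48% depends on it. But no between-patient reading tried with a medium effect reaches 80% at 30–60 patients.

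Third, 26–48% is not strictly this study's power, because a 2x2 interaction cannot be estimated from three sampled cells. This is correct. It is a further reason why the claim cannot stand, and why the H1 figures matter most.

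Fourth, the abstract and the main Discussion admit limited power and call the results hypothesis-generating, and the Sampling plan attributes the 10–20 to rarity. This lowers the risk of misreading, but it contradicts the printed figure without correcting it. The 10–30 range and the misuse of the term effect size are probably drafting slips and would be minor on their own.

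**Conclusion.** The concern holds. The statement of 80% power for a medium effect is wrong for the analysis it names: power is about 26% at 30 patients and 48% at 60, and 80% needs 128, taking medium as f = 0.25. It also concerns an analysis that is not planned. The primary test has about 30–48% power at h = 0.5 and one-sided alpha 0.05, and would need about 50 patients per group. Only very large differences are detectable: from an assumed 20% in controls to about 71% (10 per group) or 58% (20 per group). The exact risks depend on the assumed control risk, but the conclusion is the same from 10% to 30%.

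**What to change.** In the Sampling plan:

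- Delete the 2x2 ANOVA power statement and the assertion that the design secures adequate power.
- State one size throughout: 10–20 patients in each of three sampled groups, 30–60 in total. Remove the 10–30 range and the description of a patient count as an effect size.
- Say plainly that availability, not a power calculation, sets the size.
- For H1, give the detectable risk difference and the expected 95% confidence-interval width at 10 and 20 per group, for control risks of 10–30%, labelled as assumptions.

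The section will then agree with the abstract and the main Discussion. The cost is protocol wording only: no extra patients and no change to data collection. The stated power becomes less favourable.

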#### Positive controls.

Groups need to balanced in age, BMI, and in their number of follow-ups. If age between groups is unbalanced, as defined by a Cohen’s d > 0.4, outliers will be removed until this threshold is reached. For the number of follow-ups, follow-ups above the limiting factor will be ignored from the data collection to balance the groups if needed.

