## Methods

### Study design

This is a retrospective multicentric cohort study conducted at three Swiss Hospitals, Cantonal Hospital of Fribourg (HFR), University Hospital of Geneva (HUG) and University Hospital of Bern (Inselspital), to evaluate the effects of GLP-1 RA therapy on patients with IPMNs. Data from January 2010 to July 2026 will be reviewed.

The primary focus of the study will be to investigate the impact of GLP-1 RA therapy on the progression of IPMNs, specifically examining changes in IPMN radiological characteristics such as described in the Kyoto 2023 Consensus [1]. Additionally, the study will assess the variations in serum tumor markers such as CA19−9 and CEA and incidence of acute pancreatitis in patients undergoing GLP-1 RA treatment. The progression of IPMNs to high-grade dysplasia or invasive carcinoma, the need for surgical intervention or changes in IPMN surveillance protocols will also be assessed.

Data already collected from medical records, laboratory results, and imaging studies will be reviewed for patients diagnosed with IPMNs and treated with GLP-1 RAs for diabetes or obesity between 01.01.2010 and 31.07.2025 at HFR, HUG, and Inselspital. To assess the impact of GLP-1 RA exposure in patients with IPMNs, we will also include control groups without GLP-1 RA exposure and without IPMNs, resulting in four groups defined by a 2 × 2 factorial design (GLP-1 RA exposure: yes/no × IPMN: yes/no) (Fig 1).

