**Fig 1 pone.0357577.g001:**
[figure not shown]
Study design and comparison groups. Schematic overview of the retrospective multicentric cohort study evaluating the impact of GLP-1 RA therapy on patients with IPMNs. Four study groups will be included according to IPMN diagnosis and GLP-1 RA exposure: patients with IPMN treated with GLP-1 RAs, patients with IPMN not treated with GLP-1 RAs, patients without IPMN treated with GLP-1 RAs, and patients without IPMN and without GLP-1 RA exposure (general population). The primary outcome (1) is the progression of radiological IPMN characteristics according to the Kyoto 2023 Consensus criteria. Secondary outcomes include longitudinal changes in serum CA19−9 and CEA levels (2) and the incidence of acute pancreatitis (3). We hypothesize that GLP-1 RA therapy is not associated with an increased progression of IPMN radiological features or adverse pancreatic outcomes compared with patients not exposed to GLP-1 RAs.

A list of patients diagnosed with IPMNs will be compiled (List A), and this group will then be cross-referenced with data from patients who have been treated with GLP-1 RAs (List B). ICD-10 codes, keywords like IPMN and ATC medication codes will be used to identify the patients and compile the two lists (S1 File). This method will allow us to identify the subset of patients in whom both IPMN and GLP-1 RA treatment are present. The same number of patients will be randomly extracted from the two lists. For example, if 3 patients with GLP1-RA and IPMN are extracted in the HFR dataset, then 3 patients will be extracted in List A and 3 in List B. The same procedure will be carried out for the other two institutions. For the no GLP-1 RA & no IPMN group, the proportion of AP will be generalized to the incidence in the general population.

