Evaluation methods will include a review of medical records for demographic data (age, sex, BMI), clinical and family history, and comorbidities (diabetes, dyslipedmia, hypertension), along with laboratory values (lipase, amylase, HbA1c, fasting glucose, HOMA-IR, plasma insulin, C-peptide, CEA, CA 19−9). Radiological data, including data from MRI scans, will be used to monitor changes in IPMN characteristics. If only CT scans are available, they will also be evaluated, even if this is not the preferred imaging method for IPMN evaluation. Gastroenterological examination including EUS and cytological results will also be reviewed. This study adheres to the SPIRIT 2013 recommendations.

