## Discussion

This study aims to provide preliminary insights into the potential impact of GLP-1 RAs therapy on the progression and clinical outcomes of IPMNs. A better understanding of the relationship between GLP-1 RA exposure and IPMNs may help address current safety uncertainties and support clinical decision-making in this complex patient population.

Several limitations must be acknowledged. The retrospective design introduces inherent risks of selection and information bias, while the relatively small sample size limits statistical power and the ability to detect modest associations. Patient identification may be incomplete, as GLP-1 RAs prescriptions may have been initiated by healthcare providers outside the participating institutions or inconsistently documented and therefore not fully captured in institutional records. Furthermore, initiation of the treatment may have been influenced by clinical judgement and recent literature implying a possible link between GLP1 Ras use and pancreatitis or pancreatic cancer, introducing potential prescription bias. In addition, the relatively recent and rapidly increasing widespread use of GLP-1 receptor agonists may limit the ability to assess long-term effects on IPMN evolution. As a result, potential late modifications or clinically relevant changes may not yet be detectable within the available follow-up period.

Therefore, the results should be interpreted as hypothesis-generating. Despite these limitations, this study addresses an important gap in the current literature and may serve as a basis for future prospective, multicentre studies.

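### Diabetes, a reason for prescribing the drug, is neither balanced nor adjusted for, so the primary test H1 is open to confounding by indication

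*Protocol article*

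**What the plan says.** All places are in the protocol article.

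- **Indication.** Study design describes the exposed cohort as "patients diagnosed with IPMNs and treated with GLP-1 RAs for diabetes or obesity".
- **Comparators.** Study design, below the Fig 1 caption: "The same number of patients will be randomly extracted from the two lists". The draw is equal in number within each centre. No matching variable is named.
- **Balance.** Positive controls: "Groups need to balanced in age, BMI, and in their number of follow-ups". Age has a threshold (Cohen's d above 0.4) and an action, "outliers will be removed until this threshold is reached". Surplus follow-ups are dropped. BMI has neither a threshold nor an action, and diabetes does not appear.
- **Tests.** In Analysis plan, H1 compares the two IPMN groups on any Kyoto change, "as assessed by a one-sided test of two proportions". H2 is a Time by Group interaction in the same two groups. H3 is a chi-square test across three groups. No covariate or stratum is named.
- **Data.** Study design lists "comorbidities (diabetes, dyslipedmia, hypertension" among the items reviewed, and Data collection adds HbA1c and fasting glucose. No stated analysis uses them.
- **Limitation.** Discussion notes that safety literature may have influenced prescribing, "introducing potential prescription bias".

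**The concern.** Diabetes is one of the two stated reasons for giving the drug, so it should be more common in the exposed IPMN group than in a random draw of IPMN patients. If diabetes also relates to change in the lesion, it is a confounder, and nothing in the comparator draw, the balance rules or the H1 test deals with it. A positive H1 could then reflect who is prescribed the drug and not what the drug does. Because this is bias and not noise, a larger follow-on study built the same way would not remove it. That matters for a study whose declared purpose is to seed later work.

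**Working it through.** **No plan figure to reproduce.** The article gives no diabetes prevalence, progression risk or confounding estimate. Its one statistical figure, 80% power for a 2x2 ANOVA, is not an input here.

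**Inputs from the article.** Group size is 10 to 20 (Sampling plan). H1 is one-sided (Analysis plan). Alpha is 0.05 (Sampling plan).

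**Assumptions.** The drug has no effect. The risk of Kyoto change without diabetes is 20%. Diabetes multiplies that risk by RR. The share with diabetes is d1 in the exposed IPMN group and d0 in the IPMN comparators.

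**Formula.** Risk in a group with diabetes share d is p = 0.20 × [1 + d × (RR − 1)]. The crude risk ratio is p1/p0. The rejection probability comes from exact binomial enumeration of the one-sided pooled two-proportion z-test at 5%.

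**Two cases written out.**

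- 60% vs 30%, RR 1.5: p1 = 0.20 × (1 + 0.6 × 0.5) = 0.26; p0 = 0.20 × (1 + 0.3 × 0.5) = 0.23; crude risk ratio 0.26/0.23 = 1.13.
- 80% vs 20%, RR 2: p1 = 0.20 × (1 + 0.8 × 1) = 0.36; p0 = 0.20 × (1 + 0.2 × 1) = 0.24; crude risk ratio 0.36/0.24 = 1.50.

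| Diabetes, exposed vs comparator | RR | p1 vs p0 | Crude risk ratio | Rejects, n = 10 | Rejects, n = 20 |
|---|---|---|---|---|---|
| 80% vs 20% | 1.0 | 0.200 vs 0.200 | 1.00 | 4.6% | 5.1% |
| 80% vs 20% | 1.2 | 0.232 vs 0.208 | 1.12 | 6.0% | 7.3% |
| 60% vs 30% | 1.5 | 0.260 vs 0.230 | 1.13 | 6.5% | 7.9% |
| 80% vs 20% | 1.5 | 0.280 vs 0.220 | 1.27 | 8.7% | 11.7% |
| 80% vs 20% | 2.0 | 0.360 vs 0.240 | 1.50 | 14.3% | 21.2% |
| 80% vs 20% | 2.5 | 0.440 vs 0.260 | 1.69 | 21.8% | 32.4% |

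**Effect of sample size.** In the 80% vs 20%, RR 2 case, rejection at 200 per group is 84%.

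**Effect of balancing diabetes.** If d1 = d0, then p1 = p0 under no drug effect. The test rejects in about 5%, as in the first row.

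**H2 and H3.** H2 compares change within patients, so stable differences in CEA or CA19-9 between people with and without diabetes cancel. Bias needs marker trajectories that differ by diabetes. H3 includes the exposed group without IPMN, which shares the indication with the exposed IPMN group, so that contrast is much less open to the problem. The exposed-versus-unexposed contrast within H3 remains open to it.

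**The case against.** - **The obesity indication is covered.** In part. BMI is a named balance factor, so a reader who inferred that the drug cannot be separated from its indication at all would go too far. The missing BMI rule could also be a detail left to an analysis plan not shown. The firm gap is diabetes.
- **The plan does have balancing rules.** It does, for both age and number of follow-ups. It would be wrong to infer that only age has one.
- **All three tests are equally compromised.** A reader might infer this, but the designs of H2 and H3 do not support it. An unseen plan could also add covariates to H2. H1 is different, because a two-proportion test takes none.
- **Nothing in the article says diabetes drives IPMN change.** Correct. The Introduction lists new-onset diabetes only as a surveillance item. The link is an assumption, and with no link there is no bias.
- **The direction is not certain.** Discussion says safety concerns may have influenced prescribing. If that steered the drug away from higher-risk patients, it would push the other way.
- **The limits are disclosed.** Discussion admits selection and prescription bias and calls the results hypothesis-generating, which limits the consequence. However, the prescription bias it describes comes from pancreatic safety literature. It does not name diabetes as a confounder, and the H1 test is unchanged.

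**Conclusion.** The point holds for diabetes and H1. Followed exactly, the plan leaves the primary comparison open to confounding by indication, although diabetes status is already being collected. Under no drug effect and a 20% risk without diabetes, the true one-sided error at 10 to 20 per group runs from about 5% (diabetes unrelated to progression), through 6–8% (60% vs 30%, risk ratio 1.5), to 14–21% (80% vs 20%, risk ratio 2). Stronger assumptions give more. All prevalences and risk ratios are assumed, so the figures show what could happen and do not estimate what will. H2 is affected only if marker trajectories differ by diabetes, and H3 mainly in its exposed-versus-unexposed contrast. The change should be made, but the documents do not show that the study is uninformative without it.

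**What to change.** 1. **Draw.** Within each centre, draw the List A comparators frequency-matched to exposed patients on diabetes (yes/no). Add BMI or age only as far as numbers allow. Matching on all three at once within three centres would be too sparse for 10 to 20 exposed patients; the article's own example has 3 at one centre.
2. **Timing.** In exposed patients, take diabetes and BMI before GLP-1 RA initiation. T0 falls after initiation, so BMI at T0 may already reflect the drug. In comparators, take both at or before the first IPMN examination. Do not adjust for diabetes that appears later, since it may be a consequence of progression.
3. **H1.** Report a diabetes-stratified (Mantel-Haenszel) risk difference, or a Firth logistic estimate with diabetes as covariate, with a 95% CI. Keep the crude test as secondary. If the draw has already been made, this step can still be taken without a redraw.
4. **H2 wording.** Replace the causal verb linking marker change to the drug with a statement of association.

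**Cost.** A filter before the draw and one more estimate on data already collected. Intervals widen, at most one or two covariates can be supported, and a diabetes stratum with patients from only one group adds nothing to the stratified estimate. No extra patients or data are needed.

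### Age balance is obtained by deleting eligible patients until Cohen's d falls to 0.4, a rule that triggers often by chance at 10 to 20 per group and still leaves an age difference in an unadjusted primary test

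*Protocol article*

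**What the plan says.** All references are to the protocol article.

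- **Positive controls** sets the requirement: "Groups need to balanced in age, BMI, and in their number of follow-ups". For age there is a trigger, "If age between groups is unbalanced, as defined by a Cohen’s d > 0.4", and an action, "outliers will be removed until this threshold is reached".
- **Sampling plan** gives the group size: "The sample size is expected to be between 10 and 20 patients for the condition with GLP-1 RAs and IPMN". The other two sampled groups "will match in sample size the above-mentioned condition as it is the most stringent".
- **Study design** (text after the Fig 1 legend) describes how the comparison patients are obtained, centre by centre: "The same number of patients will be randomly extracted from the two lists". Age plays no part in that draw as described.
- **Analysis plan** assesses H1, the primary comparison of exposed with unexposed IPMN patients, "as assessed by a one-sided test of two proportions". No covariate is named.
- **Population** admits adults from 18 years and lists refusal of consent as the only exclusion.

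**The concern.** A patient removed under this rule meets every entry criterion, and nothing is wrong with the record. The patient goes only because his or her age pulls two group means apart. Four consequences follow.

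1. With groups this small, d exceeds 0.4 fairly often when the age distributions are the same, so patients would be lost to correct ordinary sampling variation.
2. The deletion may fall on patients with both IPMN and GLP-1 RA exposure, whom the plan itself describes as rare and whose number sets the size of the other groups.
3. Who is dropped depends on the data in hand. In a retrospective record review the outcomes may be visible at that moment, and at this size one patient can decide whether the primary test is significant.
4. Trimming stops once d reaches 0.4. The remaining age difference goes into a test that does not adjust for age, and the trimmed groups no longer represent the patients who were sampled.

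**Working it through.** The plan states no operating characteristic for the age rule, so there is no figure of its own to reproduce on this point. The power statement in Sampling plan is a separate matter, and nothing below depends on it.

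**Inputs from the document:** threshold 0.4; n = 10 to 20 per group, equal sizes; one-sided test of two proportions; alpha 0.05. **Assumptions, not in the document:** normally distributed ages; true age gaps of 0, 0.5 and 0.8 SD; 30% progression in both groups, independent of age.

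**Step 1. How often the rule triggers with no true age difference.** For two groups of size n, t = d·√(n/2) on 2n − 2 degrees of freedom. The trigger is therefore |t| > 0.4·√(n/2).

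| n per group | critical t | df | P(absolute d > 0.4) | P(signed d > 0.4) |
|---|---|---|---|---|
| 10 | 0.4·√5 = 0.894 | 18 | 38.3% | 19.1% |
| 15 | 0.4·√7.5 = 1.095 | 28 | 28.3% | 14.1% |
| 20 | 0.4·√10 = 1.265 | 38 | 21.4% | 10.7% |

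The absolute reading is the natural one for a balance check. The signed reading halves the rate.

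**Step 2. How many patients are removed.** Simulation, 3,000 runs per setting. The age extreme driving the imbalance is removed one patient at a time until |d| ≤ 0.4 (or a group is down to 3). The table takes each patient from whichever group holds the value farther from the pooled mean. Average loss = trigger rate × mean removed when triggered.

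| n per group | true gap | trigger rate | mean removed if triggered | average loss |
|---|---|---|---|---|
| 10 | 0 | 0.380 | 2.33 | 0.89 of 20 = 4% |
| 20 | 0 | 0.202 | 2.64 | 0.53 of 40 = 1% |
| 10 | 0.5 SD | 0.607 | 3.26 | 1.98 of 20 = 10% |
| 20 | 0.5 SD | 0.639 | 4.52 | 2.89 of 40 = 7% |
| 10 | 0.8 SD | 0.804 | 4.23 | 3.40 of 20 = 17% |
| 20 | 0.8 SD | 0.894 | 6.85 | 6.12 of 40 = 15% |

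A separate simulation of greedy trimming at 0.8 SD gave 3.76 of 20 (19%) and 6.11 of 40 (15%), hence the range of 15–19%. If every deletion fell on the exposed group, a chance trigger at n = 10 would remove 2.45 of its 10 patients on average, with a 90th percentile of 5.

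**Step 3. Whether one deletion can matter for H1.** Pooled z-test: z = (p₁ − p₂) / √[p(1 − p)(1/n₁ + 1/n₂)], one-sided. The starting table is an illustration chosen near the boundary.

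| exposed vs unexposed | change | z | one-sided p |
|---|---|---|---|
| 9/20 vs 4/20 | none: 0.25/0.1481 | 1.688 | 0.046 |
| 9/20 vs 4/19 | one control without progression dropped | 1.586 | 0.056 |
| 8/19 vs 4/20 | one exposed patient with progression dropped | 1.495 | 0.067 |
| 9/19 vs 4/20 | one exposed patient without progression dropped | 1.812 | 0.035 |

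**Step 4. Average effect on the test.** Three deletion orders were compared in the simulations of step 2: exposed patients only, controls only, and farthest from the pooled mean. Where the rule triggered, the orders disagreed on significance in 4–7% of data sets. Type I error was 5.0–5.4% with no deletion and about 5–6.5% under any one fixed order. Taking the most favourable of the three gave 6.9% (n = 10) and 5.7% (n = 20) with no age gap, and about 9% with a gap of 0.8 SD.

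**The case against.** The strongest reply is that the rule is stated in advance: variable, metric and threshold are all fixed in the article, and it does bring the age difference down to a cap. The article is a condensed account, so the definition of an outlier, the order of removal and any BMI procedure may stand in a fuller document. The study also calls itself hypothesis-generating and concedes selection bias and low power. Much of this stands, and it rules out several stronger readings.

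- **That the deletion is post hoc.** It is not unplanned. Only the choice of patients comes after the data are seen.
- **That the rule does nothing about confounding by age.** It reduces the imbalance but does not remove it.
- **That the rule seriously inflates type I error.** With an order fixed blind to outcome the inflation is modest. About 9% requires both a 0.8 SD gap and deliberate choice of the most favourable order. The table in step 3 was placed near 0.05, so it shows what is possible and not what is typical.
- **That the rule triggers in 65% or 43% of studies.** Those are the chance rates (10 and 20 per group) if all three sampled groups must balance pairwise. H1 compares two groups.
- **That 15–19% of patients will be lost.** This needs an age gap of 0.8 SD, for which the document gives no basis.
- **That the lack of a BMI threshold is an error.** It is a detail that may lie elsewhere.

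What the reply does not meet is the stated rule itself. A fuller definition of an outlier would make deletion reproducible, but eligible patients would still be deleted to satisfy a balance threshold. A small exploratory study has more reason to keep every patient.

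**Conclusion.** The concern holds as a badly chosen rule, not as missing detail. Followed as written, it discards eligible patients from groups of 10 to 20. With no true age difference it triggers in 38% to 21% of primary comparisons (19% to 11% if d is read as signed) and then removes about two to three patients. The average loss ranges from 1–4% to 15–19% as the assumed true gap goes from 0 to 0.8 SD. It can change a borderline primary result, and the age difference that remains is not adjusted for. The trigger rates depend only on normal ages and equal group sizes. The losses also depend on the assumed age gap and trimming order, and the error rates on the assumed 30% progression as well. Severity: should be fixed. The study is exploratory, and the defect can be repaired at the analysis stage with data already being collected.

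**What to change.** 1. Delete the outlier-removal rule. Keep every eligible sampled patient in the primary analysis.
2. Report standardised differences for age between the groups, as description and not as a trigger.
3. Adjust the H1 comparison for age, for example by penalised logistic regression or an age-stratified analysis.
4. If Lists A and B have not yet been drawn, draw the comparison patients at random within age band and centre. Adding BMI to the matching may leave too few candidates: list sizes are not given, and the article's own example has three exposed patients at one centre.
5. If trimming is still wanted, make it a sensitivity analysis under a fixed rule applied blind to outcome.

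The cost is one covariate in a small sample, a protocol change notified to the ethics committee as an amendment and, if the draw is matched, age available when the lists are compiled. Data collection was scheduled from September 2025 to March 2026, so a matched draw may come too late. Items 1 to 3 do not depend on it.
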